**Table 2 : Number of clusters necessary given different attack rates and intervention effectiveness**

| *Reduction in attack rate due to intervention* |  | *Meningitis attack rate in arm receiving standard of care (%)* | | | | | |  |
| --- | --- | --- | --- | --- | --- | --- | --- | --- |
|  |  | 0.5 | 1 | 2 | 3 | 4 | 5 | |
| 50% |  | 355 | 177 | 88 | 58 | 44 | 35 | |
| 70% |  | 157 | 79 | 39 | 26 | 20 | 16 | |
| 90% |  | 81 | 41 | 20 | 14 | 10 | 8 | |

For example, in the situation where the end-of-epidemic attack rate in villages with at least one case is 1%, and the reduction of the attack rate due to ciprofloxacin is 70%, a total of 79 villages would need to be randomized in each arm of the study.

Because of these uncertainties, the overall target sample size necessary will be set after four weeks of accumulated study data. This period is sufficiently long to allow for a description of the demographic co-factors in the study area. Table 2 shows the high variability given these co-factors, but the most likely combinations of scenarios present sample sizes that are logistically feasible.

**Resistance sub-study**

A total of 200 participants in the standard care arm and 200 participants in the community-level prophylaxis arm will be offered enrollment in the resistance sub-study. In this sub-study, a total of 3 stool samples will be collected from each participant, at Day 0, Day 7 and Day 28. Samples from Day 0 in the village-wide distribution arm will be collected prior to distribution of ciprofloxacin.

Written consent will be obtained from participants, or their parents/guardians, for participation in the resistance sub-study.

To facilitate the collection and prompt processing of the stool samples, they will be collected from 20 participants in each of 20 villages (10 villages in the standard care arm, 10 villages in the community-level prophylaxis arm.) In each of the arms, the resistance sub-study will begin once at least 10 villages have notified cases after the study start.

*Selection of villages*

Because of laboratory capacity, a maximum of two villages per day will be included in the resistance sub-study. Once the resistance sub-study has begun, the first odd-numbered village which notifies a case each day in each of the two arms will be included in the sub-study.

*Selection of participants*

In each village selected to participate in the sub-study, 20 households will be randomly selected from an exhaustive list of households in the village prepared specifically for this purpose. One member of each household will be randomly selected and will be invited to participate in the resistance sub-study. The only exclusion criteria will be if the participant knows in advance that they will be absent during the follow up visits at days 7 and 28. If this is the case, a second member of the household will be randomly selected as a replacement. Written informed consent will be obtained from each participant or their parent/guardian for participation in the resistance sub-study. Each participant will be given a unique identifier and asked whether or not they received the ciprofloxacin distribution.

*Sample collection*

In villages selected for the resistance sub-study (in both the standard care arm and community-level prophylaxis arm), participants will be identified at the time of the community sensitization messages being delivered by a study nurse in conjunction with a laboratory technician. A stool sample container will be distributed to each participant, with instructions on how to collect the sample the following morning. Study staff will then return to the village the following morning to collect the fresh stool samples. The same procedures will be followed on days 7 and 28, with one visit to provide the sample container and a second visit to pick up the fresh samples the following morning. Day 0 samples will be collected up until the time of ciprofloxacin administration in the village. At day 7 and 28, samples will also be accepted the day following the scheduled sample collection (i.e., days 8 and 29), if the participant is not able to provide a stool sample on the scheduled day.

*Sample processing*

The processing of stool samples will depend on the location of the study and its distance from the principal study lab in Maradi. The processing of samples will be detailed in the study SOPs. In brief, stool samples will be collected by study staff and either stored at 4°C or inoculated in a transport medium until reception in the central lab. Stool samples will then be plated on a MacConkey agar plate containing ciprofloxacin. After incubation, colonies will be identified using standard microbiological methods. Antibiotic resistance profiles will be determined using the disk diffusion method. The minimum inhibitory concentration (MIC) of relevant antibiotics will be determined. All identified strains will be stored in the Epicentre lab at Maradi. A total of 10% of samples will be sent to a reference laboratory for quality control purposes.

*Participant retention*

Once a participant has been included in the resistance sub-study, the study team will make every reasonable effort to ensure his or her participation for the entire study period. It is projected that attrition rate will be 25% and that up to 20% of samples will be inappropriately conserved and therefore be not able to be analyzed. The sponsor will be responsible for developing study SOPs to achieve this level of follow-up. Soap will be provided with each stool sample container so as to give sensitization messages about handwashing and to ensure that participants are able to wash their hands after sample collection (see Reimbursement below).

*Sample size considerations*

Assuming a baseline prevalence of enterobacteriaceae resistant to ciprofloxacin in the community of 20%, over three repeated visits, a sample size of 131 persons in each of the two arms would have 90% power to detect a change in the prevalence to 30%. Assuming an attrition rate of 25% and 20% of improperly collected samples, a sample size of 200 persons per arm would allow for the calculation of the primary resistance objective with sufficient power.

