**Data analysis**

The primary analysis of the difference in attack rate by study arm will be based on the overall meningitis incidence during the epidemic in villages of each arm after inclusion in the study, taking into account the cluster-randomized nature of the trial. Pairwise comparisons will be made between each intervention group using the student’s t-test. ANOVA and multiple linear regression will be used to compare the attack rates between the three study groups, and will be expressed in hazard ratios with 95% confidence intervals. The sponsor will be responsible for developing a written analytic plan.

The analysis of the resistance sub-study will be done on the basis of the per-protocol population for whom all three stool samples are available. Acquisition rates at 7 and 28 days following the initial sample will be calculated with corresponding 95% confidence intervals using the binomial distribution. The random selection of participants and households nested into a cluster-randomized design will be taken into account.

All P values will be 2-sided with *p* < 0.05 considered statistically significant. All other analyses of secondary analyses would be best regarded as exploratory, and any significant findings for these endpoints would need to be confirmed with further studies. Missing data will be assumed to be missing at random.

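### Resistance sub-study: 131 per arm matches the ordinary two-proportion size of 392 divided by three visits, and the stated 90% power is not supported by the sampling plan

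*Combined protocol and SAP*

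**What the plan says.** The Resistance sub-study section sets the design. "A total of 200 participants in the standard care arm and 200 participants in the community-level prophylaxis arm will be offered enrollment", and "a total of 3 stool samples will be collected from each participant, at Day 0, Day 7 and Day 28". For logistical reasons "they will be collected from 20 participants in each of 20 villages", which is 10 villages in each of the two arms. "Samples from Day 0 in the village-wide distribution arm will be collected prior to distribution of ciprofloxacin".

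Its sample size paragraph starts: "Assuming a baseline prevalence of enterobacteriaceae resistant to ciprofloxacin in the community of 20"%. The power claim follows: "over three repeated visits, a sample size of 131 persons in each of the two arms would have 90% power to detect". What is to be detected is worded as "a change in the prevalence to 30"%. With 25% attrition and 20% of samples lost, it concludes that 200 per arm is enough. The paragraph gives no formula, no correlation between stools from one person, and no intraclass correlation (ICC) or design effect for villages.

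The Data analysis section supplies the significance level: "All P values will be 2-sided with *p* < 0.05 considered statistically significant". For the sub-study it plans acquisition rates at Days 7 and 28 with binomial confidence intervals, among people with all three stools. It says that the nested, cluster-randomized selection will be allowed for, and leaves the written analytic plan to the sponsor.

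**The concern.** A figure of 131 per arm is far too small for an ordinary comparison of 20% with 30% at 90% power. The reference to three repeated visits suggests how it was reached: by letting each person count three times. Repeated stools from one gut over four weeks are unlikely to be independent. One of the three is taken before any drug is given, and the people come from only 20 villages.

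This matters because the Ciprofloxacin section names resistance as the main worry about mass administration. The ethics section on known and potential risks says that, if the primary result is positive, routine use will not be recommended without describing the effect on resistance. Someone who takes the sub-study to have 90% power may read too much into a finding of no clear increase.

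**Working it through.** **Inputs.** From the protocol: 20% and 30%; two-sided 5%; 90% power; 131 and 200 per arm; stools at Days 0, 7 and 28; 10 villages per arm; losses of 25% and 20%. Not in the protocol, so assumed here: the within-person correlation ρ and the village ICC for stool resistance. The only ICC given, 0.025, belongs to the meningitis endpoint and is borrowed as one value in a range.

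**1. Reproducing 131.** With pooled variance and no continuity correction:

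n = [1.960·√(2·0.25·0.75) + 1.2816·√(0.20·0.80 + 0.30·0.70)]² / 0.10² = (1.2002 + 0.7795)² / 0.01 = 391.95, so 392 per arm.

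391.95 / 3 = 130.65, so 131. The power from 3 × 131 = 393 independent stools per arm is 90.1%.

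The usual repeated-measures form is 391.95·(1 + 2ρ)/3. It gives 131 at ρ = 0, 210 at ρ = 0.3 and 262 at ρ = 0.5. Dividing by three does not give 131 if a continuity correction (138), a one-sided test (107) or 80% power (98) is used. Without the division, the smallest between-arm variant tried at 90% power is 320 (one-sided).

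**2. Power at 131 without clustering.** Power = Φ[(0.10·√(n/V) − 1.2002) / 0.6083]. Here 0.6083 = √0.37, and V is the variance relative to one stool per person.

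- One post-dose visit, V = 1: 46%.
- Mean of two independent post-dose stools, V = 0.5: 75%.

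Neither figure needs an assumed correlation other than zero.

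**3. Within-person correlation, still without clustering.** For two post-dose stools, V = (1 + ρ)/2 unadjusted, and V = (1 + ρ)/2 − ρ² when adjusted for Day 0.

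| ρ (assumed) | V unadjusted | Power | V with Day 0 | Power |
|---|---|---|---|---|
| 0.3 | 0.65 | 64% | 0.56 | 71% |
| 0.5 | 0.75 | 58% | 0.50 | 75% |
| 0.7 | 0.85 | 53% | 0.36 | 88% |
| 0.73 | 0.865 | 52% | 0.332 | 90% |

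**4. Villages.** With 131 / 10 = 13.1 evaluable people per village and a village effect that is constant over visits, add 12.1·ICC to the unadjusted V. At ρ = 0.5:

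- ICC 0.01: V = 0.871, power 52%.
- ICC 0.025: V = 1.0525, power 44%.
- ICC 0.05: V = 1.355, power 36%.

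These use a normal approximation. With 20 villages in all, true power would be slightly lower.

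**5. Losses.** 200 × 0.75 × 0.80 = 120, below 131. To keep 131 would need 131 / (0.75 × 0.80) = 218.3, so 219 per arm. Multiplying instead of dividing gives 131 × 1.25 × 1.20 = 196.5, which may be where 200 comes from; the protocol does not say. At 120, steps 2 and 3 give 43% at one visit (V = 1) and 72% from two independent post-dose stools (V = 0.5). If the 20% applies separately to each stool, 200 × 0.75 × 0.80³ = 76.8, about 77 people, have all three.

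**The case against.** The strongest reply is that no formula is printed, so the division by three is an inference. That stands. A Day 0-adjusted comparison with ρ of about 0.73 and no village effect also gives 90% at 131, as would change scores with ρ of about 0.78. These routes are less likely than 392 / 3, because the protocol states neither such a correlation nor such an analysis. None of them covers the village sampling.

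A second reply is that 200 are enrolled, not 131. Two independent post-dose stools from all 200, unclustered, would give 90.6%. That requires no losses, whereas the protocol expects to keep about 120.

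A reader might also infer more than the documents support:

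- *That true power is about half of 90%.* The figures near 40% need an assumed ρ, a borrowed ICC and an analysis that ignores Day 0. The sub-study objective is a before-and-after comparison between arms, so using Day 0 is natural; without clustering it gives 71% to 88% for ρ from 0.3 to 0.7.
- *That clustering is ignored altogether.* It is missing from the sample size only. The Data analysis section promises to allow for it.
- *That Day 0 adjustment brings one fixed gain.* At 120 evaluable, ρ = 0.5 and ICC 0.025, the village term is 11 × 0.025 = 0.275. If the village effect is constant over visits, V falls from 0.75 + 0.275 = 1.025 to 0.50 + 0.275 × 0.25 = 0.569, and power rises from 42% to 66%. If it is independent between visits, V falls from 0.75 + 0.1375 = 0.8875 to 0.50 + 0.275 × 0.75 = 0.706, and power rises from 48% to 57%.
- *That a null result would settle policy.* The ethics section asks for a description of resistance effects. The summary lists this comparison as secondary, secondary analyses are called exploratory, and the planned confidence intervals would show imprecision.

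**Conclusion.** The 90% statement is wrong as written and should be fixed. The size of 131 matches three visits counted as independent people, with the pre-dose stool included and no design effect. On stated inputs alone, unclustered power at 131 is 46% at one post-dose visit and at most 75% from an unadjusted mean of two post-dose stools. With assumed ρ of 0.3 to 0.5, it is 64% to 58% unadjusted or 71% to 75% with Day 0 adjustment. Any positive village ICC lowers these. Among the analyses checked that use post-dose stools to measure the effect, reaching 90% at 131 takes baseline adjustment, a correlation of about 0.73 or more and no village effect, none of which the protocol states. The expected 120 evaluable people make the position worse.

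How large the shortfall is depends on two correlations that the documents do not give, so it should be reported as a range. The primary meningitis comparison is not affected.

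**What to change.** - Withdraw the claim of 90% power at 131 per arm.
- Name the target comparison: resistance between arms at Day 7, Day 28 or both.
- Restate power, or the detectable difference, for 200 enrolled and about 120 evaluable per arm. Show it as a range over explicit within-person correlations and village ICCs, and say whether the 20% sample loss is per person or per stool.
- In the written analytic plan, specify a between-arm comparison of post-dose resistance that is adjusted for each participant's Day 0 result and for village clustering. The protocol names no such model for the sub-study at present, so this is an addition.

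The cost is a less favourable stated power and slightly more analysis work. No extra participants or stool samples are needed.

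### Resistance sub-study: 200 per arm does not leave the 131 the plan requires once its own losses are applied to retained participants, and the all-three-samples rule lowers the number further

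*Combined protocol and SAP*

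**What the plan says.** In the protocol's Resistance sub-study section, under Sample size considerations, the target starts from 20% resistance at baseline and counts three visits per person. It is put this way: "a sample size of 131 persons in each of the two arms would have 90% power to detect a change in the prevalence to 30" per cent. The next sentence moves to the enrolment figure: "Assuming an attrition rate of 25% and 20% of improperly collected samples, a sample size of 200 persons per arm would allow" the resistance objective to be assessed with sufficient power. The paragraph on participant retention gives the same two losses: "It is projected that attrition rate will be 25% and that up to 20% of samples will be inappropriately conserved" and so cannot be analysed.

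The sampling schedule in that section is "a total of 3 stool samples will be collected from each participant, at Day 0, Day 7 and Day 28". The 200 per arm are 20 people in each of 10 villages, and they are people to be offered enrolment.

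The Data analysis section restricts the sub-study analysis to the "per-protocol population for whom all three stool samples are available". It plans acquisition rates at 7 and 28 days after the initial sample, says the nested sampling within the cluster design will be taken into account, and assumes missing data are missing at random. No separate analysis plan is among the documents reviewed; the protocol leaves it to the sponsor to write.

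**The concern.** The plan names a required number (131), an enrolled number (200) and two losses (25% of people, 20% of samples), and then calls the enrolled number sufficient. The four figures do not fit together when the losses fall on the people who are retained.

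The analysis rule adds to this. If a person counts only when all three samples are usable, a 20% loss per sample can remove well over 20% of people.

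The sub-study carries weight. The risk section of the protocol says that even a positive primary result would not lead to a recommendation on routine use without a description of the effect on resistance. A comparison with less power than stated could miss a rise from 20% to 30% and be read as reassurance.

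**Working it through.** **Inputs.** Resistance 20% versus 30%, 90% power, 131 per arm, three samples per person, 200 per arm, 25% attrition and 20% unusable samples (Resistance sub-study). Analysis set: all three samples available (Data analysis). Alpha 0.05, two-sided, is the general rule in Data analysis ("All P values will be 2-sided"); it is not restated for the sub-study.

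**Step 1: reproduce the 131.** Pooled two-proportion formula, no continuity correction, mean proportion 0.25:

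n = [1.960 × √(2 × 0.25 × 0.75) + 1.282 × √(0.20 × 0.80 + 0.30 × 0.70)]² / 0.10² = (1.200 + 0.780)² / 0.01 ≈ 392 observations per arm.

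392 / 3 visits = 130.7, rounded up to 131. The plan's figure is reproduced. It treats a person's three samples as independent and includes no village design effect.

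**Step 2: apply the losses to 200, once per retained person.**
- Multiplied: 200 × 0.75 × 0.80 = 120.
- Added: 200 × (1 − 0.45) = 110.
- Enrolment that keeps 131: 131 / (0.75 × 0.80) = 218.3, so 219 per arm.
- A possible origin of the 200 is 131 × 1.25 × 1.20 = 196.5, which multiplies up where it should divide. This is an inference; the protocol does not show the step.

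**Step 3: apply the all-three-samples rule.** After attrition there are 150 people and 450 samples per arm, of which 20%, or 90, are unusable.
- Each spoiled sample in a different person: 150 − 90 = 60 complete.
- Spoilage concentrated, three per person: 150 − 90/3 = 120 complete.
- Independent across visits (an assumption): 150 × 0.80³ = 76.8, about 77. Keeping 131 would then need 131 / (0.75 × 0.512) = 341.1, so 342 per arm.

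**Step 4: power on the plan's own formula**, with 3 × (number complete) independent observations per arm:

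| Complete per arm | Observations | Power |
|---|---|---|
| 131 | 393 | 90.1% |
| 120 | 360 | 87.4% |
| 110 | 330 | 84.5% |
| 77 | 231 | 70.0% |
| 60 | 180 | 59.2% |

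**Step 5: how small the spoilage would have to be.** For 200 to leave 131 after 25% attrition, unusable samples could be at most 1 − 131/150 = 12.7% (applied once per person), or 1 − (131/150)^(1/3) = 4.4% (all three needed, independent losses).

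**Step 6: the same losses counted in samples, if all usable samples were analysed.** The need is 131 × 3 = 393 per arm.
- Dropouts give no sample: 450 × 0.80 = 360, power 87.4%.
- All dropouts leave after Day 0: (200 + 150 + 150) × 0.80 = 400, power 90.6%.
- All dropouts leave after Day 7: (200 + 200 + 150) × 0.80 = 440, power 93.0%.

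**The case against.** The best defence is that the 131 is really a count of samples divided by three, and the 20% is stated per sample. If dropouts give Day 0 before leaving, 400 to 440 usable samples remain against 393 needed, so 200 per arm is enough on the plan's formula. A reader might infer from the 120 and the 77 that nothing in the stated losses can reach 131. That is too strong, because this sample-level reading does reach it. About 133 or more complete participants could also remain if spoilage fell first on the dropouts' own samples, though that is an extreme and unstated assumption. The first reading does not save the sentence as written, because the all-three-samples rule excludes that analysis.

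A reader might also take 77 as the plan's own expected number. It is not: it needs losses to be independent across a person's visits, which the protocol never says. The documents support only the range 60 to 120, and the retention paragraph gives the 20% as an upper limit. The sample-size sentence does, however, adopt 20% as its planning value.

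Third, if the 20% is applied once per person, power falls only from 90% to about 87%, and the protocol attaches no separate figure to sufficient power. That is a modest loss, in a nested sub-study listed among the secondary objectives in the summary. This stands. The larger shortfall comes from joining the loss figures to the analysis rule.

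Finally, the powers describe a pooled comparison over three visits, Day 0 included, so 70% should not be read as the power of the planned acquisition analysis. This also stands.

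**Conclusion.** The statement that 200 per arm is sufficient does not follow from the plan's own figures and planned analysis set. With losses falling on retained participants, between 60 and 120 complete participants per arm are expected, against 131 required. On the plan's formula that is about 59% to 87% power against 90%, with 70% at the independence value of 77.

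This rests on three things: the 20% applied in full, attrition and spoilage not overlapping, and the complete-case rule kept as written.

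The powers are illustrative, because the formula assumes no correlation within a person or a village. As an assumption, a within-person correlation of 0.3 or 0.5 would multiply the 131 by (1 + 2ρ) and raise it to 210 or 262 before any losses. Refusals among those offered enrolment would lower the count further. The documents do not support saying that 200 per arm could never be enough: under an analysis of all usable samples it could be, on the plan's formula.

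**What to change.** Keep 200 per arm.

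1. Replace the sufficiency sentence with the expected evaluable number and power for the planned analysis set. Under the current rule this is 60 to 120 complete participants per arm, about 77 if losses are independent across visits, and about 59% to 87% power on the plan's formula.

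2. Preferably, replace the complete-case rule with an analysis of all usable samples, which fits the missing-at-random assumption already made. This would be a repeated-measures comparison of resistance prevalence by arm and visit that accounts for person and village. A person with no usable Day 0 sample cannot contribute to acquisition, so report acquisition among people with a usable Day 0 and the relevant follow-up sample, and say so.

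3. If step 2 is adopted, state the power for that set in place of the figures in step 1: about 360 to 440 usable samples per arm, depending on when dropouts leave, or about 87% to 93% on the plan's formula, noted as being before any correction for within-person and village correlation. Counts from one analysis set should not be paired with power from the other.

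The cost is a few sentences, slightly more modelling, and a stated power that is lower or more heavily qualified. No added enrolment is needed.
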